## Methods/Design

This is a prospective, randomized, single-center, controlled, exploratory intervention study with four parallel treatment groups aimed at comparing local control rates after RT with and without SIB in patients with bone metastases of the spine. Four different schedules will be evaluated: IMRT with 30 Gy in ten fractions to the whole vertebral body, IMRT with 30 Gy in ten fractions to the whole vertebral body with the application of a SIB to 40 Gy, 20 Gy in five fractions to the whole vertebral body or IMRT with 20 Gy in five fractions to the whole vertebral body with the application of a SIB to 30 Gy. Before enrolment in the study, patients will receive CT and if necessary magnetic resonance imaging (MRI)-based staging examinations to measure the spinal cord dimension. If intraspinal metastases are suspected, an MRI examination is performed beforehand.

RT is performed in systemic/targeted therapy free interval. Radiation therapy will be applied in five fractions per week (Monday to Friday).

After recording the baseline measurements, patients will be randomly assigned to one of the four groups. Target parameters will be measured and recorded at baseline (t_1_), at week 12 (t_2_), and again at week 24 (t_3_) (Fig. 1). Follow-up measurements are scheduled to take place at 12, 18, and 24 months after the completion of RT (Fig. 2).

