### Recruitment and randomization

The patients will be given all the relevant information about the study by the radiation oncologist at their first presentation to our department (approximately 1–2 weeks before the start of RT). If patients are interested in participating in the study, they will receive a second appointment in order to further inform them and to obtain informed consent. A block randomization procedure will be used to ensure even distribution of patients into the four groups. The randomization procedure will be carried out by a central office. The study personnel responsible for the recruitment and patient care will have no access to the randomization information and the study director will have no influence on the recruitment of patients. The recruitment phase will be concluded with the attainment of the planned number of patients (120 patients in total, 30 patients in each group). Projected recruitment time will be 12 months, and recruitment is scheduled to start in February 2017. Regular study follow-up will end two years after enrolment or, where applicable, with the respective patient’s death.

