### Assessment of the primary and secondary endpoints

The aim of the study is to evaluate local control rates in metastatic bone disease. The primary endpoint is defined by bone remodeling according to density in the metastasis. Bone density will be measured at the irradiated region at baseline and at the three-month time-point after the completion of RT (t_2_). Furthermore, the local control is assessed by CT imaging taken before and at three and six months after radiation treatment. Secondary endpoints are vertebral stability, QoL, fatigue, pain, overall survival, bone survival, pathological fracture, and neurological deficits. The baseline examination will be carried out immediately before the start of therapy and is scheduled to comprise the comprehensive recording of the socio-demographic data, the recording of the current pain situation (VAS score), the extent of fractures, the QoL, and the current degree of fatigue. The follow-up examinations will take place after the end of RT, as mentioned above (Fig. 1).

The secondary endpoints such as overall survival, fatigue, QoL, and anxiety will be recorded by using validated questionnaires (EORTC QLQ FA13 [14], EORTC QLQ BM22 [15], and the questionnaire to record stress in patients with cancer [FBK] according to Book et al. [16]). All patients will also be asked to record their pain history by using a pain diary (documentation of medication daily during treatment and once weekly after the completion of treatment, VAS pain scale). The pain response is documented on the VAS (range of 0–10). Complete response is defined as VAS score of 0/10 after three or six months and partial response is defined as a reduced value by at least 2 points after three or six months, according to the international consensus response categories by Chow et al. [17]. Overall survival is defined as time from initial diagnosis until death and bone survival is defined as time from initial diagnosis of irradiated spinal bone metastasis until death (Additional file 1).

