### Statistical analysis

Due to the explorative character of this study, it was not possible to estimate the total number of cases; with a scheduled number of 30 patients per group, it will, however, be possible to detect a standardized mean-value effect (Cohen’s d) of 0.74 with a power of 80% and a significance level of 5%, if a one-factorial variance analysis is calculated. All variables will be analyzed descriptively by tabulation of the measures of the empirical distributions. In case of continuous variables mean values, standard deviations, median, minimum, and maximum values will be documented. Categorical variables will be documented as occurrence and percentage. The primary endpoint will be measured by CT. Results will be presented at three months after completion of RT and differences between groups will be calculated using a one-factorial variance analysis. Differences of categorical variables will be calculated with the Chi-square test. The survival analysis will be performed using the Kaplan–Meier method and log-rank test.

All statistical analyses will be carried out descriptively using SAS software Version 9.4 or higher (SAS Institute, Cary, NC, USA).

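### Overall survival and bone survival are counted from diagnosis, not randomisation, so the curves include guaranteed survival time and the log-rank test loses power to a degree set by how much the pre-randomisation interval varies

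*Protocol article*

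**What the plan says.** Under Assessment of the primary and secondary endpoints, the article lists both survival measures as secondary: "Secondary endpoints are vertebral stability, QoL, fatigue, pain, overall survival, bone survival, pathological fracture, and neurological deficits". It then fixes the two clocks. The first is: "Overall survival is defined as time from initial diagnosis until death". The second clock has its own, different starting date: "bone survival is defined as time from initial diagnosis of irradiated spinal bone metastasis until death". The event is death in both cases.

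Under Statistical analysis, the method is: "The survival analysis will be performed using the Kaplan–Meier method and log-rank test". No delayed entry (left truncation) is mentioned.

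Randomisation comes later than either origin. Under Methods/Design: "After recording the baseline measurements, patients will be randomly assigned to one of the four groups", and the caption of Fig. 1 labels randomisation as t0. The inclusion criteria require metachronous bone lesions, so the cancer diagnosis precedes the metastasis. Under Recruitment and randomization, the trial has "120 patients in total, 30 patients in each group", and "Regular study follow-up will end two years after enrolment", or at death if earlier.

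**The concern.** A patient must be alive to be randomised. The interval from diagnosis to randomisation is therefore time in which no trial patient could have died. Plain Kaplan–Meier with the clock at diagnosis counts patients as at risk throughout that interval.

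Two things are at stake.

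- **The curves.** They mix guaranteed time before the trial with observed time in it. They do not show survival after treatment. Read as survival from diagnosis, they are too high, because patients who died before they could enrol are absent.
- **The comparison of arms.** Treatment can act only after randomisation. Adding a patient-specific interval that treatment cannot change reorders the death times and puts patients who had not yet enrolled into the risk sets. If the interval varies widely, the contrast between arms is diluted.

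Bone survival shares its event with overall survival and differs only in which earlier date starts the clock. Counted from randomisation, the two are the same endpoint.

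**Working it through.** **The plan's own power figure.** The article gives one, a Cohen's d "of 0.74 with a power of 80% and a significance level of 5"%. A two-sided two-sample t-test with 30 per group has power 0.805 at d = 0.74, and the detectable d at 80% power is 0.736, so the figure reproduces as a two-group comparison of means. It says nothing about survival. The article gives no hazard ratio, event number or power for survival.

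**Inputs from the article.** 120 patients, 30 per group; follow-up two years from enrolment; both clocks start before randomisation; Kaplan–Meier and log-rank.

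**Inputs assumed, because the article gives none.** Exponential survival after randomisation with control median 8 months; hazard ratio (HR) 0.6, or 0.5 where stated; SIB arms pooled against arms without SIB (60 versus 60) unless stated; interval from diagnosis to randomisation independent of arm; no loss to follow-up; two-sided 5%.

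**Check of the reference power (clock from randomisation).** Expected deaths by 24 months:

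- control: 60 × (1 − 0.5^(24/8)) = 52.5
- SIB: 60 × (1 − 0.5^(0.6 × 24/8)) = 42.8
- total: 95.3

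Schoenfeld's formula: power = Φ(√(D/4) × |ln HR| − 1.96) = Φ(√(95.3/4) × 0.511 − 1.96) = Φ(0.53) = 0.70. Simulation from randomisation gave 0.68 to 0.73.

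**Simulated log-rank power, HR 0.6, log-normal interval (sigma 1), 1000 trials per row.**

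| Median interval (months) | From randomisation | From diagnosis, plain | From diagnosis, delayed entry |
|---|---|---|---|
| constant 36 | 0.72 | 0.72 | 0.72 |
| 3 | 0.68 | 0.62 | 0.68 |
| 6 | 0.69 | 0.53 | 0.68 |
| 12 | 0.72 | 0.42 | 0.68 |
| 24 | 0.72 | 0.31 | 0.66 |
| 36 | 0.69 | 0.24 | 0.64 |
| 60 | 0.73 | 0.23 | 0.62 |

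**Exponential interval instead, same HR and median survival.** Power falls from about 0.70 to 0.64, 0.43, 0.26 and 0.22 for median intervals of 3, 12, 36 and 60 months. For median intervals of 1 and 2 months it moves only from 0.72 to 0.71 and from 0.71 to 0.69. The two interval shapes agree closely.

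**Four-arm log-rank, HR 0.5 in both SIB arms, log-normal interval.** 0.80 to 0.72 (median 3 months), 0.81 to 0.51 (12 months), 0.79 to 0.29 (36 months).

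**Type I error (HR 1).** About 0.05 to 0.06 with either clock, as expected: randomisation balances the interval between arms.

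**Reading the results.** The constant interval shows the mechanism. Adding the same 36 months to everyone leaves the order of deaths unchanged, so the test is unchanged, yet the whole curve shifts right by 36 months. Guaranteed time distorts the curves whatever its spread; the power loss comes from its spread relative to survival after randomisation.

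**The case against.** The strongest reply is that little depends on this. Survival is secondary, the study is called exploratory, analyses are to be carried out descriptively, no survival power is claimed, and the primary bone-density comparison is untouched. Type I error is preserved. All this stands, and it limits the severity. It does not rescue the definition: in a descriptive study the curves and medians are the main survival output, and those are what the choice of origin distorts.

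A second reply is that handling of entry times may be left to a statistical analysis plan that is not shown. Delayed entry could indeed be specified there and would recover most of the power. But the time origin is not left open; the article states it, and it is a poor origin for comparing randomised arms.

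Three stronger readings are tempting and are not supported.

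- *The test loses most of its power.* The article gives no interval distribution or survival assumption, so no single loss can be derived. The simulated range runs from nil to about two-thirds of the power.
- *Both endpoints suffer alike.* The requirement for metachronous lesions implies a gap between cancer diagnosis and metastasis, which bears on overall survival. It says nothing about the time from metastasis diagnosis to randomisation. If that is 1 to 3 months, the loss is about 0 to 7 points.
- *A median of 24, 50 or 78 months would be reported instead of 8.* That sets two time origins side by side and does not measure estimation error. In the same exponential model (median intervals 12, 36 and 60 months), the true median from diagnosis to death among enrolled controls is 24.0, 48.7 and 72.3 months, against Kaplan–Meier values of 24.0, 51.2 and 78.2. The overstatement concerns survival of all diagnosed patients, whose size the documents do not allow one to compute.

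Finally, the 60-versus-60 comparison is an assumption; the article specifies no pooling for survival. At 30 versus 30, even the clock from randomisation gives only about 42% power for HR 0.6.

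**Conclusion.** The point holds as an endpoint-definition fault of moderate severity. That both survival times include guaranteed pre-randomisation survival follows from the text alone and needs no assumption. Plain Kaplan–Meier curves on these clocks neither describe survival after treatment nor estimate survival from diagnosis without upward bias.

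The between-arm test remains valid. Its loss of power depends on inputs absent from the article. At HR 0.6, control median 8 months and 60 versus 60, it is nil for a constant interval, about 6 points at a median interval of 3 months (0.70 to 0.64), 27 points at 12 months (0.70 to 0.43) and 44 points at 36 months (0.70 to 0.26). A large loss is plausible for overall survival from cancer diagnosis. A small one is likely for bone survival, provided metastases are irradiated soon after they are found.

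**What to change.** 1. Define overall survival as time from randomisation to death from any cause, censored at last contact alive, and use it for all between-arm Kaplan–Meier and log-rank analyses.
2. Do not test bone survival separately between arms, since from randomisation it is identical to overall survival.
3. If survival from cancer diagnosis or from metastasis diagnosis is wanted, report it descriptively with delayed entry at randomisation.

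The cost is a change of endpoint wording. Randomisation is already a named time-point (t0 in Fig. 1), so no new assessment is needed. The downside is less direct comparison with series that count from diagnosis, which item 3 partly meets.

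### Bone survival and overall survival count the same deaths and differ only by an interval fixed before randomisation, so bone survival says nothing about failure of the irradiated bone

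*Protocol article*

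**What the plan says.** All the definitions are in the protocol article, under Assessment of the primary and secondary endpoints.

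- Aim: "The aim of the study is to evaluate local control rates in metastatic bone disease".
- Primary endpoint: "The primary endpoint is defined by bone remodeling according to density in the metastasis", measured at baseline and three months after radiotherapy.
- Local control: "the local control is assessed by CT imaging taken before and at three and six months after radiation treatment".
- Secondary endpoints: "Secondary endpoints are vertebral stability, QoL, fatigue, pain, overall survival, bone survival, pathological fracture, and neurological deficits".
- Overall survival: "Overall survival is defined as time from initial diagnosis until death".
- Bone survival: "bone survival is defined as time from initial diagnosis of irradiated spinal bone metastasis until death".

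Under Statistical analysis, time-to-event methods appear once: "The survival analysis will be performed using the Kaplan–Meier method and log-rank test". For the rest, the primary endpoint has a one-factor analysis of variance, and "Differences of categorical variables will be calculated with the Chi-square test".

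Follow-up runs to two years after enrolment or to death (Recruitment and randomization). Visits are planned at 12, 18 and 24 months after radiotherapy (Methods/Design).

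**The concern.** Overall survival and bone survival are listed as two separate endpoints, but both end at the same death. The second has a name that a reader will connect with the treated bone, yet nothing that happens to that bone can end it. A patient whose vertebra collapses at two months and who dies at two years gets the same bone survival as one with the same dates and an intact vertebra.

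A Kaplan–Meier curve headed bone survival could be read as durability of local control. The article's Discussion invites that comparison, since it cites a 24-month local control rate of 93% from an earlier series of stereotactic treatment with an integrated boost. The bone survival curve would not be comparable with that figure. A boost effect on the bone that does not change mortality cannot appear in it.

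**Working it through.** The plan gives no number for these endpoints, so there is none to reproduce. Its one design figure (standardised effect 0.74, 30 per group, 80% power) concerns a comparison of means and does not enter here.

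**Step 1. The definitions side by side**

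| | Overall survival | Bone survival |
|---|---|---|
| Start | initial diagnosis (read as the primary tumour) | diagnosis of the irradiated spinal metastasis |
| Event | death, no cause restriction | death, no cause restriction |
| Patients | all randomised | all randomised |

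**Step 2. Algebra.** For one patient let A be the date of initial diagnosis, B the diagnosis of the irradiated metastasis, R randomisation and D death.

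- Overall survival = D − A.
- Bone survival = D − B.
- Difference = (D − A) − (D − B) = B − A.

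D cancels. Because A and B both precede R, B − A is a baseline characteristic that treatment cannot alter. The event indicator is the same for both endpoints, as is the date of censoring for a patient still alive. Bone survival therefore adds no post-randomisation information to overall survival.

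Both durations also contain time before randomisation: R − A in one and R − B in the other. An enrolled patient could not have died in that time and treatment could not act in it. Survival from randomisation would be D − R.

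**Step 3. Which bone events count?** Let F be the date of local progression, fracture or neurological deficit at the irradiated level. F appears in neither formula, so the number of bone failures counted as bone survival events is zero, whatever the true failure rate.

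**Step 4. Are the two tests the same?** The starts differ by an amount that varies between patients (the inclusion criteria ask for metachronous lesions), so the risk sets differ. A simulation shows how much this can matter. None of its rates come from the documents:

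- two groups of 60, for example boost against no boost;
- exponential survival, median 10 months from randomisation, with 24 months of follow-up;
- exponential intervals with mean 3 months from metastasis diagnosis to randomisation and mean 36 months from primary diagnosis to metastasis diagnosis;
- 4,000 runs for each hazard ratio.

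| Quantity | Result |
|---|---|
| Deaths, hazard ratio 1 | mean 97 of 120, shared by both endpoints by definition |
| Correlation of log-rank Z, overall survival with bone survival, hazard ratio 1 | 0.54 |
| Correlation of log-rank Z, bone survival with survival from randomisation, hazard ratio 1 | 0.97 |
| Power at hazard ratio 0.6, overall survival from initial diagnosis | 33% |
| Power at hazard ratio 0.6, bone survival | 64% |
| Power at hazard ratio 0.6, survival from randomisation | 66% |

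The deaths are shared, but the test results are not copies. On these assumptions bone survival behaves almost like survival from randomisation. Overall survival from initial diagnosis loses power because the long and variable time before randomisation is included.

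**The case against.** The best defence is that the definition is explicit and consistent: it states a start and an event, and nowhere says that it measures local failure. On that view only the label is at fault. The treated bone is also followed elsewhere, through density at three months, CT local control at three and six months, vertebral stability, fracture and neurological deficit. Rates at fixed visits suit an aim worded as local control rates, and progression seen on CT is dated only to the visit. The article condenses a fuller protocol that may specify more.

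Much of this stands, and it rules out three stronger readings.

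- **That the two log-rank results are near copies.** Step 4 shows they need not be. Only the events are the same.
- **That failure of the irradiated bone goes unrecorded.** It does not. The patient with the collapsed vertebra should appear under fracture and stability.
- **That the background frequencies in the article (fracture 5%, cord compression 10–15%) give a count of ignored failures.** They carry no time frame and no link to irradiated vertebrae. Metastatic spinal cord compression is excluded at entry, and fractures and neurological deficits are endpoints in their own right.

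What the defence does not remove is the definition itself. It is printed in full, so the point does not rest on something an article would leave out. The fixed-time outcomes also fill the gap only in part. A patient who dies before the three- or six-month CT has no reading, and each way of counting such a patient distorts a simple proportion. A local-control reading at three and six months does not use the later follow-up.

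**Conclusion.** The point holds in a limited form. Overall survival and bone survival share every event, and their difference is fixed before randomisation. Bone survival counts no failure of the irradiated bone. As described in the article, the local-control aim rests on fixed-time or categorical assessments, which deal poorly with deaths in a palliative population.

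The exact part (same deaths, no bone events) follows from the definitions. It rests only on reading death without qualification as death from any cause, and initial diagnosis as that of the primary tumour. The correlations and powers depend on assumed rates and serve only to show that the two tests can differ.

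The consequence is modest. These are secondary endpoints of an exploratory study, and the primary endpoint, the sample size and the main comparison are unaffected. The change is still worth making, because the label bears on the trial's central question and could be misread in the results.

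**What to change.** 1. Keep one overall survival endpoint, counted from randomisation to death.
2. Rename the present bone survival as survival since diagnosis of bone metastasis, or drop it.
3. Add time from randomisation to first local failure of the irradiated vertebra, meaning the first of local progression on CT, pathological fracture, or new neurological deficit attributable to that level. Treat death without local failure as a competing event and report cumulative incidence by arm.
4. Optionally report a composite that also counts death, with a table of first events by component. It should not be the main local endpoint: in the Step 4 simulation with no treatment effect, 97 of 120 patients (97/120 = 81%) died within follow-up, so deaths would tend to dominate it.

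The cost is more than rewording, but small. The outcomes are already named in the plan. What has to be added is a CT criterion for progression, event dates, and a link from each fracture or deficit to the irradiated level. Local failures will be few with 30 patients per arm, and progression found on CT is dated only to the scheduled scan, so the comparison remains exploratory.

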### Radiotherapy

Treatment will be planned three-dimensionally using CT scan with a 3-mm slice thickness taken across the involved vertebral region. Immobilization is ensured with an Aquaplast head mask (Aquaplast Corporation, Wyckoff, NJ, USA), vacuum mattress, and Wingstep® (Elekta, Stockholm, Sweden). On the basis of the planning CT, organs at risk will be contoured. The spinal cord is contoured on the basis of visible target on the CT scan with the help of fusion with the MRI data.

The SIB includes the macroscopic tumor. Gross tumor volume (GTV) includes the metastasis. GTV plus 3-mm safety margin gives CTV. CTV corresponds to planning target volume (PTV).

The GTV includes the macroscopic metastatsis. The CTV covers the entire vertebral body including posterior structures (pedicles, processi, and arcus). The CTV with an addition of 3 mm produces PTV. The PTV includes the tumorous vertebra will be covered by the 90% isodose.

Radiation will be applied as IMRT (tomotherapy or step-and-shoot IMRT or volumetric modulated arc therapy [VMAT], energy of 6 MV) using 30 Gy in ten fractions, or 30 Gy in ten fractions and SIB to 40 Gy in ten fractions, or 20 Gy in five fractions, or 20 Gy in five fractions and SIB to 30 Gy. Tolerance doses of the organs at risk are based on the data published for the RTOG 06-31 study [18].

